### Economic analysis

A within trial cost-utility analysis will be conducted to compare the Mitii™ intervention to usual care from both a health care and societal perspective. The costs and outcomes for each group will be compared using incremental cost-effectiveness ratios (ICERs) (i.e. [cost Mitii™ – cost waitlist/ [QALYs Mitii™ – QALYs waitlist].

The CHU-9D will be scored using the Australian preference weights and total QALYs estimated for the period of the trial [151]. Key variables (e.g. cost of delivering the intervention, scoring the CHU-9D with the UK preference weights) will be altered and tested in one-way and multi-way sensitivity analyses to generate a range of possible ICERs for the intervention. Economic data will be bootstrapped to generate 95 % CI.

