**Methods/Design:**

Sixty independently ambulant children (30 in each group) at least 12 months post ABI will be recruited to participate in this trial. Children will be matched in pairs at baseline and randomly allocated to receive either 20 weeks of Mitii™ training (30 min per day, six days a week, with a potential total dose of 60 h) immediately, or be waitlisted for 20 weeks. Outcomes will be assessed at baseline, immediately post-intervention and at 20 weeks post-intervention. The primary outcomes will be the Assessment of Motor and Process Skills and 30 s repetition maximum of functional strength exercises (sit-to-stand, step-ups and half kneel to stand). Measures of body structure and functions, activity, participation and quality of life will assess the efficacy of Mitii™ across all domains of the International Classification of Functioning, Disability and Health framework. A subset of children will undertake three tesla (3T) magnetic resonance imaging scans to evaluate functional neurovascular changes, structural imaging, diffusion imaging and resting state functional connectivity before and after intervention.

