### Secondary hypotheses

Compared to usual care, Mitii™ training will achieve significantly greater:Upper limb activity (unimanual and bimanual), as measured on the Jebsen-Taylor Test of Hand Function (JTTHF), MUUL and the Assisting Hand Assessment (AHA) [56];Lower limb gross motor capacity assessed using the Timed Up and Go (TUG) test, 6-min Walk Test (6MWT) and the High-Level Mobility Assessment Tool (HiMAT);Habitual physical activity (as measured on the ActiGraph® accelerometer) [57];Neurovascular (functional MRI) changes;Visual perception (visual discrimination, visual memory and visual sequential memory) measured on the Test of Visual Perception Skills (TVPS) [58];Executive functioning including information processing, attentional control, cognitive flexibility, goal setting, working memory and behavioural manifestations in everyday life as measured by subtests from the Delis-Kaplan Executive Function System (D-KEFS), the Wechsler Intelligence Scale for Children Fourth Edition (WISC-IV), the Comprehensive Trail Making Test (CTMT), Tower of London – Second Edition and the Behaviour Rating Inventory of Executive Function (BRIEF);Attention including performance on tasks of attention (TEA-Ch) and attention in everyday life as measured by parent rating (Conner’s 3);Psychological functioning as measured by the Strengths and Difficulties Questionnaire (SDQ);Performance and satisfaction with occupational performance goals using the COPM;Participation as measured by the Child and Adolescent Scale of Environment (CASE) and Child and Adolescent Scale of Participation (CASP);QOL on the domains of functioning and participation as measured on the Kidscreen-52;Parent reported functional abilities in self-care and daily activities (using the MobQues28) [59]

Finally, Mitii™ will be more cost-effective compared with usual care as shown by resource use and consequence based on function (AMPS) and QOL (Child Health Utility 9D (CHU-9D) [60] and Kidscreen-52 [61])

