### Design

This study utilises a matched-pairs, randomised waitlist controlled trial (see Fig. 1 for CONSORT flow chart). A matched pairs design was chosen to minimise the risk of baseline between-group differences. A waitlist design ensures that all participants have access to this novel intervention and will facilitate recruitment into the study. Within each pair, each participant will be randomised into either:*Immediate intervention group:* Families return home with Mitii™ equipment and commence training immediately for 20 weeks and then Mitii™ is withdrawn; or*Waitlist delayed intervention (control) group:* Families continue care as usual for 20 weeks, return to Brisbane for a one day re-assessment and then return home with Mitii™ equipment to commence training for 20 weeks. Care as usual includes any therapies (for example, occupational therapy and physiotherapy) usually provided by public or private services and visits to their treating paediatrician or general practitioner. Information about each participant’s usual care during the study period will be gathered using a general study questionnaire. After re-assessment the participants (and their family) will receive the Mitii™ introduction and equipment ready to commence training.

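### The ICER is the only stated economic comparison measure, but it loses the sign of the QALY difference and breaks down near zero, so read alone it may not support the cost-effectiveness hypothesis

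*Protocol article*

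**What the plan says.** The Economic analysis section plans a within-trial cost-utility analysis from health care and societal perspectives. It fixes one comparison measure: "The costs and outcomes for each group will be compared using incremental cost-effectiveness ratios (ICERs"), with the ratio written out as "cost Mitii™ – cost waitlist/ [QALYs Mitii™ – QALYs waitlist". Sensitivity analyses, including a change from Australian to UK preference weights for the CHU-9D, take the form of "one-way and multi-way sensitivity analyses to generate a range of possible ICERs for the intervention". On uncertainty the section has one sentence: "Economic data will be bootstrapped to generate 95 % CI". It does not say which quantity the interval is for.

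The Secondary hypotheses section ends with a directional claim: "Mitii™ will be more cost-effective compared with usual care as shown by resource use and consequence based on function (AMPS) and QOL", QOL being measured by the CHU-9D and the Kidscreen-52.

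The abstract sets the size: "Sixty independently ambulant children (30 in each group) at least 12 months post ABI will be recruited to participate in this trial". The Design section sets the length of the randomised contrast for the waitlist group: "Families continue care as usual for 20 weeks, return to Brisbane for a one day re-assessment", after which that group starts Mitii.

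The protocol states no willingness-to-pay threshold and no rule for calling Mitii cost-effective. It does not say what will be reported if the QALY difference is zero or negative.

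**The concern.** An ICER is a ratio of two signed differences. Once the ratio is formed, the sign of its denominator cannot be recovered. A negative ICER can mean the best outcome (cheaper and better) or the worst (costlier and worse). As the QALY difference passes through zero, the ratio jumps between minus and plus infinity. Bootstrap replicates on both sides of zero therefore cannot be ranked from favourable to unfavourable by the size of the ratio, and limits taken from such a ranking are hard to interpret.

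This trial is exposed to the problem. The groups are small, and the period in which only one group has Mitii is short. Mitii adds trainer time and equipment while other usual-care therapies may continue, so higher cost with an uncertain QALY gain is a realistic result. What is at stake is the reading of the final secondary hypothesis. The primary outcomes are not affected.

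**Working it through.** **The plan's own figures.** The economic section gives no sample size or precision. The trial was sized on function: AMPS process scale, difference 0.30 and SD 0.40; sit-to-stand, difference 4 and SD 5. With 80% power and α = 0.05, a two-sample t calculation gives 28.9 and 25.5 per group, rounded up to the stated 29 and 26. Both reproduce. Neither concerns QALYs.

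**Sign ambiguity (no assumption about this trial is needed).** ICER = ΔC/ΔQ. Net monetary benefit NMB = λ·ΔQ − ΔC, here with an illustrative λ = 50,000 per QALY.

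| ΔC | ΔQ | ICER | NMB |
|---|---|---|---|
| +1,000 | −0.01 (Mitii dominated) | −100,000 | −1,500 |
| −1,000 | +0.01 (Mitii dominant) | −100,000 | +1,500 |
| +1,000 | +0.01 | +100,000 | −500 |
| −1,000 | −0.01 | +100,000 | +500 |

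The ICER cannot separate the first two rows or the last two. Net benefit separates both pairs.

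**Sensitivity range.** Suppose ΔC stays at +1,000 and a change of preference weights moves ΔQ from +0.005 to −0.005. The ICER goes from +200,000 to −200,000. Read as a range, this spans zero and every value between, although no scenario lies there.

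**How close to zero the QALY difference may be.** The protocol gives n = 30 per group and a 20-week window, 20/52 = 0.385 year. Assumed, because the protocol gives no values: a utility SD of 0.10 to 0.20, and a utility difference that builds linearly from zero.

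- A 20-week utility difference of 0.05 is worth 0.05 × 0.385/2 = 0.0096 QALY.
- QALY SD = utility SD × 0.385/2 = 0.0192 to 0.0385.
- SE of the difference = SD × √(2/30) = 0.0050 to 0.0099; 95% half-width (1.96 × SE) = 0.0097 to 0.0195.
- With a true difference of +0.0096, the estimate is negative with probability Φ(−0.0096/SE) = about 3% to 17%. With a true difference of zero it is negative half the time.

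The same normal approximation applies to the bootstrap. If the estimate is +0.0096, about 3% to 17% of replicates have a negative QALY difference. When Mitii costs more, these costlier-and-worse replicates have negative ratios and sort to the low, apparently favourable end. They already exceed the 2.5% that a percentile interval cuts off, so the lower limit would come from them.

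**Illustrative simulation.** 400 trials per scenario, 1,000 resamples each, 30 per group, extra cost 1,000 per child, λ = 50,000, and the utility assumptions above. The first two result columns apply a rule that is not in the protocol.

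| True 20-week utility difference | ICER < λ | Whole percentile ICER interval < λ | NMB > 0 | NMB interval above 0 |
|---|---|---|---|---|
| 0 | about 51% | 2.5–4.5% | 0–2% | 0% |
| −0.05 to −0.10 | 84–100% | 15–97% | 0–0.3% | 0% |

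A repeat of the zero-effect case with 3,000 trials gave about 3% for the whole interval.

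**The case against.** A reader might infer that the trial will declare Mitii cost-effective whenever the ICER, or its upper limit, falls below a threshold, and that it would then often make a false claim. The documents do not support this. They contain no threshold and no such rule, so the simulated percentages describe a rule supplied for illustration. Even under that rule, the whole interval seldom misleads when there is no QALY effect. The high rates need a true QALY loss: a utility deficit of 0.05 to 0.10 by week 20.

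The bootstrap sentence names neither the ICER nor percentile limits. It could mean intervals for costs and QALYs separately, which would be sound. Both differences must be computed before any ratio, so the analyst will know their signs. The hypothesis itself speaks of resource use together with function and QOL, not of a ratio alone. A condensed article may also leave a cost-effectiveness plane, an acceptability curve or a threshold range to a fuller economic plan, and their absence is no error.

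All of this stands, and it limits the size of the point. It does not remove it. The article goes beyond leaving the measure open: it names the ICER for the main comparison and again for the sensitivity analyses, and no other economic estimate appears to which the interval could belong. Nothing in the section commits to reporting the separate differences or dominance.

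**Conclusion.** The point holds as a weakness in the named measure. The ICER is the sole stated measure for comparing costs and QALYs; it cannot distinguish dominant from dominated results and has no value at a zero QALY difference. That part is algebra.

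That the problem may well arise here rests on 30 per group, a 20-week contrast and the assumed utility SD of 0.10 to 0.20, under which a 0.05 utility gain (0.0096 QALY) is no larger than the 95% half-width (0.0097 to 0.0195). An ICER or its interval read alone may then not support the cost-effectiveness hypothesis. That the interval is for the ICER is the most natural reading, not a stated fact.

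It is not shown that the trial would reach a false conclusion at any particular rate. The point concerns one secondary hypothesis and can be settled in wording.

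**What to change.** In the Economic analysis section:

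- Report incremental cost and incremental QALYs, each with a bootstrap 95% CI, and say which quantity every interval is for.
- Base the cost-effectiveness conclusion on incremental net monetary benefit, λ·ΔQ − ΔC, with its bootstrap 95% CI over a stated range of λ. Add a cost-effectiveness plane or acceptability curve from the same replicates.
- Summarise the sensitivity analyses as net benefit or as pairs of differences, not only as a range of ICERs.
- Where one arm is both cheaper and better, say so by name instead of printing a negative ICER.

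The cost is that a threshold range must be chosen and stated in advance. The data and the bootstrap replicates stay the same, and no further children or assessments are needed.

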### MRI analysis

#### Structural parcellation

Cortical reconstruction and volumetric segmentation will be performed using the MPRAGE images with the Freesurfer image analysis suite (http://surfer.nmr.mgh.harvard.edu). Briefly, non-brain tissue will be removed using a hybrid watershed/surface deformation procedure [157]. Subcortical white matter and deep grey matter volumetric structures will be segmented automatically and intensity inhomogeneity of the images will be corrected [158, 159]. The cerebral cortex will be parcellated into 34 units per hemisphere based on gyral and sulcal structure [160, 161]. In addition to cortical regions, the left and right thalamus, left and right cerebellum and brain stem will be extracted. The accuracy of the cortical and subcortical parcellation will be assessed visually. An axial slice will be manually defined below the inferior most slice on which the pons was visible to include only the most caudal part of the brain stem.

A termination mask will be generated to prevent diffusion tractography streamlines from crossing the cortical folds as described previously [162]. Briefly, the interface between white matter and grey matter will be identified and this boundary shifted one voxel into the grey matter. Streamlines will be terminated when penetrating more than one voxel deep into grey matter.

#### Diffusion processing

An extensive pre-processing procedure will be followed to detect and correct for image artefacts caused by involuntary head motion, cardiac pulsation and image distortions [163]. In brief, images with within-volume movement will be detected using the discontinuity index and excluded from further analysis [164]. Image distortions caused by susceptibility in homogeneities will be reduced using the field map, employing FUGUE and PRELUDE tools available with FSL and intensity in homogeneities will be removed using n3 correction [165, 159]. Subsequently, signal intensity outlier voxels (caused by cardiac pulsation, head motion and other artefacts) will be detected and replaced using DROP-R [166]. DROP-R will be modified from the originally proposed method to employ a higher order model of the diffusion signal suitable for the detection and replacement of outliers in high b-value diffusion data (HOMOR) [167]. Between-volume registration to account for head movement during the scan time will be performed using FMAM with adjustment of the b-matrix [168–170] . Following these steps, fractional anisotrophy (FA) will be estimated from the corrected diffusion data. Constrained spherical deconvolution (http://nitrc.org/projects/mrtrix) will be employed to estimate the fibre orientation distribution for tractography at maximum harmonic order [85, 171].

#### Connectome construction

Diffusion and structural data will be co-registered using a rigid-body transformation with FLIRT (part of FSL) by registering the FA to the skull-stripped MPRAGE [165]. Registration accuracy will be checked visually. Five million probabilistic streamlines will be generated, seeding throughout the entire brain volume, to produce a whole brain tractogram. Streamlines will be prevented from crossing cortical folds by applying the termination mask generated from structural data (see section Structural parcellation). Cortico-cortical, cortico-thalamic, cortico-cerebellar and cerebello-cerebellar connections will be extracted from the whole brain tractogram by hit-testing both terminal end points of every streamline with every cortical and cerebellar region. For brain stem connections, only one terminal endpoint will be required to reside within the cortical, thalamic or cerebellar region, with any part of the streamline passing through the brain stem. For every possible link between any pair of nodes, the number of connecting streamlines will be noted. Median FA values will be calculated by sampling the diffusion maps at every step of the selected streamlines. Connections with fewer than 250 streamlines (average) in children with typical development will be excluded from further analysis (threshold determined empirically). Results will be recorded in enriched connectivity matrices.

#### Statistical analysis of the brain network

Statistical analysis of the brain network will be performed using the network based statistic toolbox for Matlab (https://sites.google.com/site/bctnet/comparison/nbs) [172]. A general linear model will be used to identify differences in FA between participant groups for every connection, using age as a confounding variable.

## Discussion

This proposed study presents the background and design for a matched pairs, randomised waitlist controlled trial comparing 20 weeks of intensive Mitii™ training to usual care for children with an ABI. This study is the first to investigate the effects of a multi-modal training program delivered over the internet compared to usual care and will also be the largest of its type in this population. Furthermore, we will be evaluating outcomes of the Mitii™ training program across all domains of the ICF using the most valid and reliable assessment tools available for use. We anticipate that the results of this study will be disseminated through peer reviewed journals and national and international academic conferences.

## Abbreviations

ABI: Acquired brain injury
ADHD: Attention deficit hyperactivity disorder
ADL: Activities of daily living
AHA: Assisting hand assessment
AMPS: Assessment of motor and process skills
AROC: Australasian rehabilitation outcome centre
BGBS: Basal ganglia and brainstem score
BIM: Bimanual training
BM: Brain maldevelopment
BMI: Body mass index
BoNT-A: Botulinum toxin serotype A
BOT-MP: Bruininks-oseretsky test of motor proficiency
BRI: Behavioural regulation index
BRIEF: Brief rating inventory of executive functioning
CAI: Centre for advanced imaging
CASE: Child and adolescent scale of environment
CASP: Child and adolescent scale of participation
CDGM: Cortical and deep grey matter
CHU-9D: Child health utility 9D
CI: Confidence interval
COPM: Canadian occupational performance measure
CP: Cerebral palsy
CSD: Constrained spherical deconvolution
CTMT: Comprehensive trail making test
D-KEFS: Delis-kaplan executive function system
dMRI: Diffuse magnetic resonance imaging
DT: Duel task
EPI: Echo-planar imaging
ET: Echo time
FC: Functional connectivity
fMRI: Functional magnetic resonance imaging
FOV: Field of view
FSIQ: Full scale intelligence quotient
GCS: Glasgow coma scale
GEC: Global executive composite
GEEs: Generalised estimating equations
GMFCS: Gross motor functional classification system
GMFM: Gross motor function measure
GRE: Gradient-recalled-echo
GS: Global score
HiMAT: High-level mobility assessment tool
HPA: Habitual physical activity
HS: Hemispheric score
ICC: Intraclass correlation coefficients
ICERs: Incremental cost-effectiveness ratios
ICF: International classification of functioning, disability and health
IQ: Intelligence quotient
JTTHF: Jebsen taylor test of hand function
KM: Krägeloh-mann
LI: Laterality index
LOA: Limits of agreement
LOC: Loss of consciousness
MACS: Manual ability classification system
MCI: Metacognition index
mCIMT: Modified constraint induced movement therapy
MDC: Minimum detectable change
METS: Metabolic equivalents
Mitii™: Move it to improve it
MUUL: Melbourne assessment of unilateral upper limb function
MRI: Magnetic resonance imaging
M2PD: Moving two point discrimination
PEDI: Pediatric evaluation of disability inventory
PEM-CY: Participation and environment measure for children and youth
PRI: Perceptual reasoning index
PSI: Processing speed index
PTA: Post-traumatic amnesia
PWM: Periventricular white matter
QALYs: Quality adjusted life years
QCPRRC: Queensland cerebral palsy and rehabilitation research centre
QOL: Quality of life
QPRS: Queensland paediatric rehabilitation service
RCT: Randomised controlled trial
Rep_max_: Repetition maximum
ROM: Range of motion
RT: Repetition time
SD: Standard deviation
SDQ: Strengths and difficulties questionnaire
SEM: Standard error of measurement
sMRI: Structural magnetic resonance imaging
TEA-Ch: Test of everyday attention for children
TBI: Traumatic brain injury
TDC: Typically developing children
TMS: Transcranial magnetic stimulation
TOL: Tower of london
TUG: Timed up and go
TVPS: Test of visual perceptual skills
UL: Upper limb
VCI: Verbal comprehension index
VR: Virtual reality
WeeFIM: Functional independence measure for children
WHO: World health organisation
WISC-IV: Wechsler intelligence scale for children–fourth edition
WM: Working memory
3T: 3 tesla
6MWT: 6-minute walk test
